#### 2.3.6 Vascular function

Vascular function will be assessed by measuring the carotid-femoral pulse wave velocity (cfPWV), carotid-radial pulse wave velocity (crPWV), the central augmentation index (CAIx) and other hemodynamic parameters, the cardio ankle vascular index (CAVI) and the brachial-ankle pulse wave velocity (baPWV). cfPWV, crPWV and CAIx will be estimated using a SphygmoCor device (AtCor Medical Pty Ltd, central office, West Ryde, Australia). The pulse waves of the carotid, radial and femoral arteries will be analysed, with the patient in the supine position, estimating the delay time with respect to the r wave of the electrocardiogram (ECG) and calculating the cfPWV and crPWV. The distance measurements will be recorded using a measuring tape from the sternal notch to the carotid and femoral arteries and carotid and radial arteries, i.e., where the sensor will be. We will calculate the Arterial Stiffness Gradient Using the ratio of carotid-femoral pulse wave velocity (PWV) to carotid-radial PWV (Fortier and Agharazii, 2016; Pereira et al., 2021). With the patient in a sitting position and leaning his/her arm on a rigid surface, the pulse waves will be analysed with a sensor on the radial artery, using a mathematical transformation to estimate the aortic pulse wave and CAIx (Boutouyrie and Vermeersch, 2010).

CAVI and baPWV will be estimated using a VaSera VS-2000 device (Fukuda Denshi Co, Ltd, Tokyo, Japan), following the manufacturer’s instructions. The values of CAVI will be automatically calculated by replacing the parameters of stiffness in the following equation to detect the vascular elasticity and caPWV: stiffness parameter β=2 ρ × 1/(Ps–Pd) × ln (Ps/Pd) × PWV, where ρ is blood density, Ps and Pd are PAS and PAD in mmHg, respectively, and VOP is measured between the aortic valve and the ankle. The electrodes will be connected to the right and left arms and ankles, and a cardiac sound microphone will be fixed with double-sided adhesive tape to the sternum by the second intercostal space. The participants will remain still and quiet for 5 minutes. Only the CAVI measurements obtained during at least 3 consecutive heartbeats will be considered valid (Shirai et al., 2011). baPWV will be estimated using the following equation: baPWV= (0.5934 × height(cm)+14.4724)/tba, where tba is the time interval between brachial waves and ankle waves (Yamashina et al., 2002; RVfAS, 2010). The CAVI values will be classified as: normal (CAVI<8), borderline (8≤CAVI <9) and abnormal (CAVI≥9) (Shirai et al., 2011; Kawai et al., 2013).

#### 2.3.7 Vascular ageing

Vascular ageing will be evaluated with cfPWV, baPWV or vascular age estimated using a VaSera VS-2000 device (Fukuda Denshi Co, Ltd, Tokyo, Japan) as measures of arterial stiffness. Firstly, the subjects who present vascular injury (injury in the carotid artery or peripheral arteriopathy) will be classified as EVA. Secondly, the subjects will be classified as EVA, NVA and HVA if the values of cfPWV or baPWV are above percentile p90, between p10 and p90, and below p10, respectively. (Gomez-Sanchez et al., 2020)

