**Methods:** This cross-sectional, descriptive, observational study will be carried out in the Primary Care Research Unit of Salamanca (APISAL) and in the BioSepsis laboratory of the University of Salamanca. The sample will be selected from the persistent COVID monographic office at the Internal Medicine Service of the University Hospital of Salamanca, and from the population of subjects diagnosed with persistent COVID in the clinical history of Primary Care. Through consecutive sampling, the study will include 300 individuals diagnosed with persistent COVID who meet the diagnosis criteria established by the WHO, after they sign the informed consent. Endothelial damage biomarkers will be measured using ELLA-SimplePlexTM technology (Biotechne). Their vascular structure and function will be analysed by measuring the carotid intima-media thickness (Sonosite Micromax); the pulse wave and carotid-femoral pulse wave velocity (cfPWV) will be recorded with Sphygmocor System^®^. Cardio Ankle Vascular Index (CAVI), brachial-ankle pulse wave velocity (baPWV) and ankle-brachial index will be analysed with Vasera VS-2000^®^. The integral assessment of the subjects with persistent COVID will be conducted with different scales that evaluate fatigue, sleep, dyspnea, quality of life, attention, nutrition state, and fragility. We will also evaluate their lifestyles (diet, physical activity, smoking habits and alcohol consumption), psychological factors, and cognitive deterioration, which will be gathered through validated questionnaires; moreover, physical activity will be objectively measured using a pedometer for 7 days. Body composition will be measured through impedance using an Inbody 230. Vascular ageing will be calculated with 10 and 90 percentiles of cfPWV and baPWV. Furthermore, we will analyse the presence of vascular injury in the retina, heart, kidneys and brain, as well as cardiovascular risk. Demographic and analytical variables will also be gathered.

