The alteration in the structure of the vascular wall evaluated with carotid artery ultrasound and ankle-brachial index (ABI) along with AS have been used as biomarkers to improve the prediction of cardiovascular risk (Visseren et al., 2021). AS presents with a decrease of artery elasticity, and it is a predictor of risk of cardiovascular diseases of similar or greater importance with respect to other traditional cardiovascular risk factors (Visseren et al., 2021). Thus, AS measured in a non-invasive manner, with carotid femoral pulse wave velocity (cfPWV), brachial-ankle pulse wave velocity (baPWV), and cardio-ankle vascular index (CAVI), has shown a positive association with cardiovascular events (Ohkuma et al., 2017; Zhong et al., 2018; Matsushita et al., 2019; Miyoshi et al., 2021; Yasuharu et al., 2021). AS is mainly determined by age, sex and arterial pressure (Laurent et al., 2019; Visseren et al., 2021). In this way, when the central arteries become more rigid, they maintain their duct functions, although they progressively lose their storage properties (Williams et al., 2018a). AS is related to cardiovascular risk factors, lifestyles, inflammatory factors, and psychological factors (Avolio, 2013; Tsai and Hsu, 2021). Therefore, its detection can play an important role in the prevention of cardiovascular diseases, as its alteration appears before the vascular structure is affected (Williams et al., 2018a). Currently, we can measure vascular structure and function in a non-invasive manner. cfPWV, measured with tonometry, is considered the measure of reference (Williams et al., 2018a). cfPWV depends on the arterial pressure at the time of the measurement, and it reflects the AS of the descending aorta, iliac arteries, the first portion of the femoral arteries, the brachiocephalic trunk, and the common carotid artery, without evaluating the ascending aorta, and it is a measure of central AS (Boutouyrie and Vermeersch, 2010). baPWV, measured by oscillometry, is a measure of peripheral AS (Munakata, 2016). CAVI, also evaluated through oscillometry, analyses the stiffness of the aorta (including the ascending aorta) and the iliac, femoral and tibial arteries; it does not depend on the arterial pressure at the time of the measurement, and it is considered a measure of both central and peripheral AS (Shirai et al., 2011; Namba et al., 2019). AS is associated with the appearance of vascular ageing (Nowak et al., 2018; Laurent et al., 2019), reflecting the dissociation between the chronological and biological age of the major arteries, with their alteration preceding the appearance of cardiovascular events (Williams et al., 2018a; Nowak et al., 2018; Laurent et al., 2019). Vascular ageing is used for the early identification of subjects that could benefit from primary prevention. It is described as a gradual process that involves biochemical, enzymatic and cellular processes in the vascular area combined with epigenetic and molecular alterations, and it is considered that it is a fundamental reflection of biological ageing in general, and a determinant of vascular functioning (Mikael et al., 2017; Nowak et al., 2018). During the last decades, epidemiological studies have been conducted to unravel the determining factors of vascular ageing, drawing great interest, as it shows a stronger relationship with morbimortality by cardiovascular diseases than biological ageing (Nowak et al., 2018; Laurent et al., 2019). In this sense, it is known that early vascular ageing (EVA), normal vascular ageing (NVA) and healthy vascular ageing (HVA) are related to the progression of the deleterious characteristics of arterial functioning, which is influenced by the genetic background, the prevalence of classic cardiovascular risk factors, lifestyles and inflammatory factors (Niiranen et al., 2017; Botto et al., 2018; Ji et al., 2018; Nilsson et al., 2018; Nowak et al., 2018; Foscolou et al., 2019). The effect of physical activity on vascular ageing has been analysed in numerous studies, confirming that it plays an important role by mitigating vascular ageing, increasing the availability of nitric oxide (NO) and reducing oxidative stress and vascular wall inflammation (Andersson et al., 2015; Antunes et al., 2016; Jakovljevic, 2018; Zhang et al., 2018; Kucharska-Newton et al., 2019; Gomez-Sanchez et al., 2020). However, some authors suggest that this effect is different between sexes (Seals et al., 2019) and varies depending on the type of physical activity performed (Li et al., 2015). The benefits of the Mediterranean diet (Martinez-Gonzalez et al., 2019; Papadaki et al., 2020; Liu et al., 2021; Morze et al., 2021) and the influence of smoking habits and alcohol consumption on cardiovascular diseases (Kondo et al., 2019; Gonzalez-Sanchez et al., 2020) is widely demonstrated. Lastly, the psychological factors can worsen the inflammatory response or increase the blood levels of cortisol (Shah et al., 2011). Thus, different psychological components such as anxiety, depression and chronic stress can enhance vascular ageing. Nevertheless, the relationship among the determining factors of vascular ageing continues to be an area of interest for research (Gomez-Sanchez et al., 2022). Therefore, maintaining a process of NVA is fundamental for preserving vascular health and delaying the appearance of cardiovascular diseases (Mikael et al., 2017; Nowak et al., 2018). Currently, there is no consensus on a definition of vascular ageing. In this regard, several authors have defined HVA, excluding hypertensive or diabetic subjects from the group of HVA (Niiranen et al., 2017; Ji et al., 2018; Nilsson et al., 2018), and using the percentiles of cfPWV below 10 or 25 from a reference population, or from their own study population, stratified by age groups, and some authors also take into account the values of arterial pressure. Different definitions of EVA have also been published (Van Bortel et al., 2012; Cunha et al., 2015; Cunha et al., 2017; Botto et al., 2018), which are gathered in several studies that consider the highest percentiles of cfPWV for its definition. Various works have employed the values published by Boutouyrie et al. in a European population as reference values (Boutouyrie and Vermeersch, 2010). Our research group has recently published reference values of the different measures of AS for the Spanish adult population without previous cardiovascular disease (Gómez-Sánchez et al., 2020a). Furthermore, we have analysed AS in a general population without cardiovascular disease, measured with several parameters and using different criteria of vascular ageing, analysing their relationship with lifestyles, cardiovascular risk factors, inflammatory factors and psychological factors (Gómez-Sánchez et al., 2020b; Gomez-Sanchez et al., 2020; GómezSánchez et al., 2020). Therefore, we consider that the best definition of vascular ageing must be that which considers the following variables: age, arterial pressure and sex (i.e., the variables with greatest influence on AS), as well as the percentiles of cfPWV of the study population.

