
To sum up, persistent COVID may affect the entire spectrum of COVID-19 patients, from those with a very mild acute disease to those who are seriously ill. The symptoms are heterogeneous, including fatigue, post-effort discomfort, dyspnea, cognitive deterioration, sleep disorders, anxiety and depression, muscle pain, brain fog, anosmia/dysgeusia, headache and limitation of the functional capacity, which affect the quality of life of the patients. The relationship between AS and vascular ageing is not clear. The starting hypothesis of this study states that individuals diagnosed with persistent COVID present greater alteration in the vascular structure and function, as well as worse vascular ageing, compared to the general population without a diagnosis of persistent COVID, since the vascular system of these people is subjected to complex inflammatory deregulation, which has not been studied to date.

Therefore, the main objectives of this study are: 1) to analyse vascular structure, vascular function, biomarkers of endothelial damage and ageing in Spanish adults diagnosed with persistent COVID, determining the differences between sexes; and 2) to analyse the association of the clinical symptoms, lifestyles (physical activity, diet, alcohol consumption and smoking habits), and psychological, cognitive and inflammatory factors with biomarkers of endothelial damage, vascular structure, function and ageing, determining the differences by sexes. Regarding the secondary objectives of this study, we will analyse the possible differences among individuals with persistent COVID according to whether the infection is caused by the Delta mutation or the Omicron mutation. Furthermore, in order to continue advancing in the recognition and visibility of the patients affected by persistent COVID, they will be given a voice through a focal discussion group, where we will delve into the opinions and experiences of the population to facilitate the transfer of the study to the habitual clinical practice.

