## 2 Methods and analysis

### 2.1 Study design and context

This will be a cross-sectional, descriptive, observational study in which we will analyse vascular structure, function and ageing and biomarkers of endothelial damage, and their relationship with lifestyles and psychological and inflammatory factors in adults with persistent COVID. The discussion groups will investigate the opinions and experiences of what the affectation by persistent COVID posed to these patients. The Persistent COVID study (GRS 2501/B/22) was registered in ClinicalTrials.gov (registration number: NCT05819840) in April 2023. In order to know if the subjects with persistent Covid have the parameters of structure, of vascular function, as well as the degree of altered vascular aging, we will use as a reference group, the values of these parameters available in the results of the EVA Study in the general population without previous cardiovascular disease (Gómez-Sánchez et al., 2020a), and we will also compare the results with other reference populations (Determinants of pulse wave velocity, 2010; Engelen et al., 2013; Herbert et al., 2014; Cunha et al., 2015). The study will be developed in the Primary Care Research Unit of Salamanca (APISAL) during the year 2023. In this period, we will select the sample and gather the data through questionnaires and explorations, which are described below. This project was approved by the ‘Ethics Committee of Research with Medicines of the health area of Salamanca’ on 27/06/2022 (CEIm reference code: Ref. PI 2022 06 1048). The SPIRIT verification list (Standard Protocol Items: Recommendations for Interventional Trials) (Chan et al., 2013) is available for this protocol (Supplementary Material S1).

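### The article gives conflicting sources for the p10/p90 cut-offs that class vascular ageing, and its operative rule names no age or sex strata and can place one subject in two classes

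*Protocol article*

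**What the plan says.** Four places in the protocol article bear on the classification into early, normal and healthy vascular ageing (EVA, NVA, HVA).

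- **Section 2.3.7, the operative rule.** Step one: "Firstly, the subjects who present vascular injury (injury in the carotid artery or peripheral arteriopathy) will be classified as EVA". Step two: "the subjects will be classified as EVA, NVA and HVA if the values of cfPWV or baPWV are above percentile p90", between p10 and p90, or below p10. The section gives no source population and no strata. It cites an earlier paper by the group.
- **Section 1, Introduction.** After noting that other authors took percentiles either from a reference population or from their own sample, it concludes that "the best definition of vascular ageing must be that which considers the following variables: age, arterial pressure and sex", and in the same sentence adds "as well as the percentiles of cfPWV of the study population".
- **Section 2.1.** The EVA Study in the general population is the reference group for vascular structure and function, "as well as the degree of altered vascular aging". Other reference populations will also be compared. Nothing says that p10 and p90 are taken from there.
- **Abstract.** "Vascular ageing will be calculated with 10 and 90 percentiles of cfPWV and baPWV".

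The starting hypothesis in section 1 is that patients have altered vascular structure and function, "as well as worse vascular ageing, compared to the general population without a diagnosis of persistent COVID".

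**The concern.** Vascular ageing is part of both main objectives, and the hypothesis compares it with the general population. Whether the class shares can speak to that comparison depends on where p10 and p90 come from. The article leans one way in the Introduction and another in section 2.1, and section 2.3.7 does not settle it.

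Three things are at stake:

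1. Cut-offs from this sample make the class shares at the percentile step a constant.
2. Cut-offs without age strata make the classes largely a proxy for age. That matters for objective 2, where symptoms, lifestyle and biomarkers are related to vascular ageing.
3. The word that joins cfPWV and baPWV in section 2.3.7 does not give mutually exclusive classes.

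If these choices are left open until data are in hand, the EVA share depends on which reading is taken.

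**Working it through.** **Inputs.** From section 2.2: cfPWV difference 0.35 m/s, SD 2.1, two-sided alpha 0.05, beta below 0.2, required 283, planned 300. From section 2.3.7: p10 and p90. Assumptions, not in the article: normal distributions with the same SD in patients and reference; cfPWV–baPWV correlation 0.5 to 0.7; age explaining 20% to 50% of cfPWV variance; prevalence of vascular injury 5% to 20%, independent of stiffness.

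**The article's own figure.** A one-sample comparison with a fixed reference mean needs n = (SD × (z0.975 + z0.80) / difference)² = (2.1 × (1.960 + 0.842) / 0.35)² = 282.6, so 283. The stated figure reproduces, and only in this form: a two-sample comparison would need 566 per group. The sample size is therefore built on the mean of cfPWV against an external value, not on the class shares.

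**Own-sample percentiles.** By definition 10% of the sample lies above its own p90 and 10% below its own p10, which is 30 and 30 of 300 per measure. Simulated samples of 300 gave 10.0% EVA at true shifts of 0, 0.35 and 2.1 m/s alike. Age and sex strata do not change this: each stratum then has 10% by construction, so the EVA share at this step could not differ between the sexes either.

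**Reference percentiles.** P(EVA) = 1 − Φ(1.2816 − shift/2.1).

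| True shift (m/s) | 1.2816 − shift/2.1 | EVA, reference p90 | EVA, own p90 |
|---|---|---|---|
| 0 | 1.282 | 10.0% | 10% |
| 0.35 | 1.115 | 13.2% | 10% |
| 0.7 | 0.948 | 17.2% | 10% |
| 1.0 | 0.805 | 21.0% | 10% |

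Even with reference cut-offs the class share is a weaker measure than the mean. At n = 300, a one-sample test of 13.2% against 10% has about 47% power, against about 82% for the 0.35 m/s difference in mean cfPWV.

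**Pooled cut-offs (section 2.3.7 read literally).** Write standardised cfPWV as √R² × age + √(1 − R²) × remainder and apply one p90 to everyone.

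| R² (assumed) | EVA, youngest third | EVA, oldest third | Of those classed EVA, also above p90 for their age |
|---|---|---|---|
| 0.2 | 2.8% | 19.5% | 68% |
| 0.5 | 0.4% | 25.7% | 47% |

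**Joining the two measures.** A subject above p90 on cfPWV and mid-range on baPWV satisfies the EVA condition through one measure and the NVA condition through the other. With correlation 0.5 to 0.7 (bivariate normal), the two measures put a subject in different classes in 27% to 21% of cases, about 81 to 64 of 300. If EVA means either measure above p90, the percentile step gives 16.8% to 15.3% EVA in a wholly normal population.

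**Adding the injury step.** Total EVA = v + (1 − v) × percentile share. With one measure, v = 0.05 gives 0.05 + 0.95 × 0.10 = 14.5%, and v = 0.20 gives 0.20 + 0.80 × 0.10 = 28%. The fixed 10% applies to the percentile step on a single measure, not to the total.

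**The case against.** The strongest reply is that the external comparison is already planned. Section 2.1 names the EVA Study as reference and includes the degree of vascular ageing, section 2.4 adds Z scores for comparison with reference populations, and the study is sized on mean cfPWV against Spanish reference data. This stands. A reader might infer that the plan cannot show worse vascular ageing at all, or that total EVA is fixed near 10%. The article supports neither: the injury step and an either-measure reading both move the total, and the mean and Z-score comparisons do not use the classes.

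A second reply is that the Introduction sentence cannot be used by halves, since it asks for age, arterial pressure and sex as well as study-population percentiles. This also stands. The absence of strata describes section 2.3.7, not the authors' stated preference. The own-sample and pooled problems are therefore two separate readings, not one combined rule. But stratifying does not rescue own-sample cut-offs for the population comparison.

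Third, the strata and percentile source may be in the cited paper or the full protocol, neither of which is shown. That would excuse silence. It does not remove the different directions given in the Introduction and section 2.1.

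Fourth, section 2.4 plans covariance and regression adjustment, so the association analyses need not reduce to age. This is fair, although adjusting a model does not correct a label already assigned by a pooled cut-off.

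Finally, a reader might infer from the Abstract a rule that both measures must exceed p90, contradicting section 2.3.7. The Abstract's wording reads as a list of the measures used, so no such contradiction is claimed here.

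**Conclusion.** The concern holds in a limited form. The Introduction, section 2.1 and section 2.3.7 do not agree on which population supplies p10 and p90 or on whether age, sex and arterial pressure enter, and the rule in section 2.3.7 is not mutually exclusive.

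Under the own-sample reading, the percentile step carries no information about the general-population comparison. This follows from the definition of a percentile and needs no assumption. The signal lost is a rise from 10% to about 13%, 17% or 21% EVA for shifts of 0.35, 0.7 or 1.0 m/s, given normality and a common SD of 2.1. Under the pooled reading, EVA would be about 0.4% to 3% in the youngest third and 20% to 26% in the oldest, given the assumed 20% to 50% of variance explained by age.

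This should be corrected before analysis, but it does not defeat the study, because sections 2.1 and 2.4 already give an external route for the main comparison.

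**What to change.** In section 2.3.7:

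1. State that, for comparison with the general population, p10 and p90 are the age- and sex-specific EVA Study values. Reconcile the Introduction sentence with this, including whether arterial pressure enters the definition.
2. Limit any study-population percentiles to within-sample association analyses, stratified or adjusted by age and sex.
3. Classify cfPWV and baPWV separately, or state one combination rule that puts each subject in exactly one class.
4. Apply the same vascular-injury step to the reference participants, or compare only the percentile-step proportions.

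The cost is wording and a little extra programming; by the Introduction's account, the group has itself published reference values for the Spanish adult population. Making cfPWV the only primary classifier, or a continuous Z score the main vascular-ageing outcome for objective 2, is a reasonable preference but is not needed to resolve the conflict.
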